### Outcomes

Following written informed consent and full eligibility assessment, all eligible patients will be assessed on all outcomes before randomisation (‘baseline’), after the 8-week intervention period (‘post-intervention’), and after a 6-month and 12-month follow-up periods (‘follow-up’) by blinded assessors (see Fig. 1). Secondary outcomes and process measures using the Experience Sampling Method (ESM) will be assessed at baseline, post-intervention, and 6-month follow-up.

#### Primary outcomes

The primary outcome of the study is distress associated with psychotic experiences measured with the mean distress score of the CAARMS positive symptom subscale (range 0–100) [1]. The CAARMS is a semi-structured interview, which is sensitive to change [33] and shows a high reliability [53].

#### Secondary outcomes

The secondary outcomes of the study are global and social functioning, (momentary) psychotic experiences, and psychopathology. Measures to assesses secondary outcomes will include the Global Assessment of Functioning (GAF) [54] scale, the Social and Occupational Functioning Assessment Scale (SOFAS) [55], and the Social Functioning Scale (SFS) [56] to assess global and social functioning. In addition, the Experience Sampling Method (ESM), a structured, random time-sampling diary technique will be used to measure activities and social contacts ten times per day over a period of six consecutive days using an established ESM data collection protocol on a smartphone-based app (the PsyMate™ app) [22–24, 57–60] in order to assess momentary social functioning [61]. Secondary outcome measures will further include the Brief Psychiatric Rating Scale (BPRS) [62] and the Brief Negative Symptom Scale (BNSS) [63] to cover the full range of psychotic experiences and psychopathology as well as the CAARMS and Positive and Negative Syndrome Scale (PANSS) [64] for a-priori planned subgroup analyses in UHR and FEP participants. Also, psychopathology will be assessed in daily life with ESM (including momentary psychotic experiences and momentary negative affect).

#### Process measures

Process measures to assess putative mechanisms of change will include ESM measures of minor stressors, negative affect, pleasantness of events, and positive affect to assess stress sensitivity (operationalised as an increase in negative affect in response to minor stressors) and reward experience (operationalised as an increase in positive affect in response to pleasant events) at baseline, post-intervention, and 6-month (and – for non-ESM measures – 12-month) follow-up [22–24, 57–60]. Psychological flexibility operationalised as the six core ACT competences (see above) will be measured using the Acceptance and Action Questionnaire [65, 66], the Five Facet Mindfulness Questionnaire [67], the Flexibility Index Test [68], and the ESM. Cognitive flexibility will be measured using the PSYRATS to assess belief flexibility [69], the beads task to assess reasoning bias [70], and experimental Experience Sampling Methodology (eESM) task for measuring liberal acceptance bias [71]. In addition, the Temporal Experience of Pleasure Scale (TEPS) [72] will be used to assess anticipatory and consummatory pleasure and, more broadly, reward experience. The therapeutic alliance will be assessed using the Working Alliance Inventory [73, 74] and will involve clinician and patient ratings. In addition, the app-based EMI of ACT-DL will provide detailed process measures of mood, psychotic experiences and activities in the experimental condition.

#### Acceptability, treatment adherence and treatment fidelity

Acceptability of ACT-DL will be assessed at post-intervention through a questionnaire asking participants to evaluate ease of use, accessibility and comprehensiveness of various components of the intervention. The app-based EMI of ACT-DL will further provide detailed data on treatment adherence to ACT-DL (e.g. number of exercises completed per week). Treatment fidelity will be rated based on a random selection of audio tapes of three training sessions recorded by clinicians delivering ACT-DL using an ACT-DL adherence checklist covering all core ACT and EMI components [46].

#### Other measures

Other measures will assess socio-demographic characteristics, alcohol/substance use (Composite International Diagnostic Interview [75], MINI [50]), current and past medication use, and IQ (Dutch Adult Reading Test [76]) as potential confounders that may be associated with primary and secondary outcomes. Service use will be assessed using a therapy classification checklist. Also, personality (Eysenck Personality Questionnaire [77]), trait anxiety (State-Trait Anxiety Inventory [78]), depression (Beck Depression Inventory-II [79]), psychotic experiences (Prodromal Questionnaire Long Version [80]), attachment (Psychosis Attachment Measure [81]), and childhood trauma (Childhood Trauma Questionnaire [82]) will be assessed.

### Sample size

Previous studies suggest that third-wave CBT [40, 83, 84], including ACT [40, 44], may yield reductions in psychotic experiences of moderate to large effect size. Consistent with previous research [44], the power calculation is based on the primary outcome of a reduction in distress associated with psychotic experiences of moderate effect size (i.e. in line with Gaudiano and Herbert [44]) measured with the CAARMS. Power simulation in R indicates that a sample size of *n* = 150 participants (75 experimental, 75 control condition) will be sufficient to test our primary hypothesis of the effect of condition (ACT-DL + TAU vs. TAU) on distress associated with psychotic experiences at all three time points (i.e. post-intervention, 6-month and 12-month follow-ups), which will be tested using an omnibus test of no difference between the two conditions at all three time points against the two-sided alternative hypothesis that there is a difference at one (or more) of the three follow-up time points, while controlling for baseline distress associated with psychotic experiences. Specifically, we expect an attrition rate of 31%, resulting in a loss to follow-up of 23 individuals per condition on average. Hence, we will recruit a total sample of *n* = 150 participants (75 per arm) at baseline to the study, which allows for a 31% attrition rate and leaves *n* = 104 participants to detect a medium effect size of *d* = 0.5 at (at least) one of the post-intervention and follow-up time points, with a power of 0.92 when testing at alpha = 0.05. Power simulation further indicates that a sample of 150 participants, will be sufficient to detect a large effect size (Cohen’s *d* = 0.8) at *p* < 0.05 for the difference in the effect of condition on distress associated with psychotic experiences between FEP and UHR with a power of 0.75 at post-intervention and follow-up in a-priori planned subgroup analysis, while allowing, again, for a 31% attrition rate (notably, given the power calculation expected this attrition rate to be constant at all three time points and not to increase – as is expected – over time (see Fig. 1), power was under-estimated for this secondary analysis). Hence, this sample size will allow us to test the secondary hypothesis whether there is a clinically meaningful difference (of large effect size) between FEP and UHR that would be relevant to be considered in the implementation of ACT-DL in routine care for these patient groups.

### Randomisation and blinding

Participants will be randomised at a 50:50 ratio to the experimental or control condition at the level of the individual participant by an independent researcher through a computer-generated sequence following informed consent, full eligibility assessment, and assessment of all outcome measures. Block randomisation will be carried out in blocks of six participants, with stratification for the five centres (Amsterdam, The Hague, Maastricht/Eindhoven, Flemish-Brabant, East/West Flanders) and two groups of UHR and FEP (expecting a 50:50 ratio of UHR and FEP to be included in the sample). The researchers will be blind to the allocation of participants to the experimental and control group of the study. There will be a contact person for any questions regarding the procedure that is not involved in any testing to allow researchers to be blind towards the allocation of participants when assessing outcomes. Any breaks in blindness will be documented and another researcher will be allocated to complete the next set of assessments where possible.

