### Participants

The study will aim to recruit 150 participants with UHR or FEP from secondary mental health services at clinical sites of five centres: (1) Amsterdam (Academic Medical Centre, Arkin Basis GGZ), (2) The Hague (Parnassia/PsyQ), (3) Maastricht/Eindhoven (Mondriaan, Virenze, GGZE) (all in the Netherlands), (4) Flemish-Brabant (Leuven (UPC KU Leuven), Antwerp (VDIP), Diest (Sint-Annendael), Mortsel (PCM)), and (5) East/West Flanders (Brugge (OLV), Melle (Karus), Sint Niklaas (VDIP)) (all in Belgium). Individuals receiving care from these secondary mental health services will be approached by a clinician of these services, who will provide initial information about the study. Individuals, who are interested to take part in the study, will be asked for their consent to be approached by a member of the research team to learn more about the study. If the potential participant agrees, they will be fully informed about the study in a face-to-face session or on the phone by a researcher and, after 1 week, asked for written informed consent. Full eligibility assessment will be conducted by the researcher once participants have provided written informed consent, which can be withdrawn at any time without any negative consequences for participants. Participants will be rewarded financially for complete participation, and travel expenses will be fully reimbursed.

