#### Experimental condition: ACT-DL + TAU

Participants allocated to the experimental condition will receive ACT-DL with trained clinicians within an 8-week period in addition to TAU, which will consist of all the treatment that they received prior to the start of the study and include all the input from their general practitioner, psychiatrist, and other members of the mental health care team that they would receive if they did not participate in the study, with the exception of manualised CBTp. The intervention can be discontinued by participants at any time upon request without any negative consequences.

The manualised ACT-DL intervention consists of eight ACT training sessions (including one session for psychoeducation) administered face-to-face by a trained clinician (i.e. psychologists having received a 5-day training in ACT-DL and receiving fortnightly supervision sessions for the purposes of the trial), each for around 45–60 min, and an ACT-based EMI, which participants will receive following randomisation to the experimental condition [46], over an 8-week intervention period. The latter will be administered through a smartphone-based app (i.e. the PsyMate™ app) to allow participants to apply the skills that they have been trained into their daily lives [28–30]. The first six face-to-face ACT sessions are based on a modified version of ACT for people with psychosis [35, 43, 44, 51] and aim to enhance participants’ psychological flexibility by training them in six core components: creative hopelessness, acceptance, cognitive defusion, self as context and contact with the present moment, values, and committed action [46, 52]. In the last session, all six components will be integrated and reviewed.

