The main effect of condition will be tested via an omnibus test of no difference between the two conditions at all three time points (Wald-type test with df = 3 and alpha = .05). Should the omnibus test be statistically significant, then the three time-specific contrasts will be examined to determine at which time points significant differences are present (each tested at alpha = .05). Secondary hypotheses and analyses of process measures to assess putative mechanisms of change will be tested following the same steps. Given that block randomisation will be carried out in blocks of six participants, with stratification for centre and group, all analyses will include centre and group as covariate, even though there is little reason to expect noteworthy clustering of outcomes by centre.

In addition, multilevel mediation analysis will be used to test indirect effects of condition on primary outcomes (distress associated with psychotic experiences) and secondary outcomes (psychotic experiences, psychopathology, social functioning) via pathways through putative mechanisms of change (psychological flexibility, stress sensitivity, reward experience). Multilevel mediation models will be fitted in MPlus, Version 7 [90], to control for within-subject clustering of multiple time points [91, 92], using the MLR estimator, which allows for the use of all available data under the assumption that data is missing at random (if all variables associated with missing values are included in the model). In a two-level model, multiple time points (level 1) will be treated as nested within subjects (level 2). The total effect of condition (level 2) on primary/secondary outcomes (level 1) will be apportioned into direct and indirect (or, synonymously, mediating) effects through putative mechanisms of change (level 1) using the product of coefficients strategy. This strategy quantifies the point estimate of the indirect effect as the product of the coefficient of independent variable on mediator variable (path a) and the coefficient of mediator variable on dependent variable (path b). We will use statistical software by Selig and Preacher [93] for computing Monte Carlo confidence intervals and assessing the statistical significance of indirect effects, given their advantages over rival methods in the context of multilevel mediation models [93, 94].

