## Trial status

This trial is ongoing. The trial started recruitment in November 2016 and recruitment and outcome assessment will continue until June 2020. The results will be published in peer-reviewed journals in 2020.

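### A single fixed block size of six within centre-by-group strata makes some allocations predictable to staff who track them, leaving a modest risk of selective or timed referral

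*Protocol article*

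**What the plan says.** *Randomisation and blinding* (protocol article) sets 1:1 individual randomisation by an independent researcher from a computer-generated sequence, after consent, eligibility assessment and baseline measures. It adds: "Block randomisation will be carried out in blocks of six participants", "with stratification for the five centres" and for UHR versus FEP. *Statistical analysis* repeats the single size: "Given that block randomisation will be carried out in blocks of six participants, with stratification for centre and group". Neither section mentions varying the size or keeping it from sites.

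Under *Participants*, patients in the services "will be approached by a clinician of these services, who will provide initial information about the study". A researcher then gives full information, takes consent after a week and assesses eligibility. The researchers are to be blind to allocation. No such statement covers the treating services.

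*Experimental condition: ACT-DL + TAU* describes eight face-to-face sessions plus an app, with usual care continuing "with the exception of manualised CBTp". *Trial status* says the trial is ongoing and that "recruitment and outcome assessment will continue until June 2020".

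**The concern.** With one constant block size, the end of each block is determined by what came before. Blinded assessors and an independent sequence holder do not fully close this gap, because the first step towards enrolment is taken by service clinicians. Those clinicians will probably know which of their patients attend ACT-DL sessions or fall under the CBTp exclusion. If they can anticipate the next arm, they can influence whom they refer and when.

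Bias of that kind arises before randomisation, so blinded outcome assessment cannot remove it. The planned adjustment for baseline distress, centre and group covers only those variables. It does not cover selection on, for example, engagement or expected response.

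**Working it through.** The plan gives no figure for predictability, so there is none to reproduce.

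**Inputs**
- Block of six, 3:3 (*Randomisation and blinding*).
- Strata: 5 centres × 2 groups = 10.
- N = 150 (*Sample size*). Equal strata are an assumption: 150 / 10 = 15 per stratum, or 15 / 6 = 2.5 blocks.
- Services listed per centre (*Participants*): Amsterdam 2, The Hague apparently 1, Maastricht/Eindhoven 3, Flemish-Brabant 4, East/West Flanders 3.

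**Worst case, one complete block.** The observer knows the size, the boundaries and all earlier allocations, and always guesses the arm with more places left. All 20 possible 3:3 sequences are equally likely.

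| Position | P(allocation certain) | P(guess correct) |
|---|---|---|
| 1 | 0 | 0.5 |
| 2 | 0 | 3/5 = 0.6 |
| 3 | 0 | 0.4 × 3/4 + 0.6 × 1/2 = 0.6 |
| 4 | 0.1 | 0.1 × 1 + 0.9 × 2/3 = 0.7 |
| 5 | 0.4 | 0.4 × 1 + 0.6 × 1/2 = 0.7 |
| 6 | 1 | 1 |
| Sum | 1.5 | 4.1 |

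Certain: 1.5 / 6 = 25%. Correct guesses: 4.1 / 6 = 68.3%.

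**Worst case, 15 per stratum.** This is two complete blocks plus the first three positions of a third.
- Certain: (2 × 1.5 + 0) / 15 = 20%, or 0.20 × 150 = 30 participants over the trial.
- Correct guesses: (2 × 4.1 + 0.5 + 0.6 + 0.6) / 15 = 9.9 / 15 = 66%.

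**Partial view.** Here a clinician sees only the earlier allocations at their own service, one of K equally likely services in the centre, and guesses whichever arm that service is behind on. Simulation of 10,000 strata of 15 for each K gave:

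| K | Correct guesses |
|---|---|
| 1 | 66% |
| 2 | 56.0% |
| 3 | 54.6% |
| 4 | 53.5% |

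This is one simple guessing rule, not a proven optimum.

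**Effect of varying the size.** Simulation of 3,000 strata of 15 for each scheme. The observer knows all earlier allocations and the set of possible sizes, and guesses optimally.

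| Block sizes | Certain | Correct guesses |
|---|---|---|
| 6 only | 20% | 66.1% |
| 4, 6 | 5.7% | 67.6% |
| 4, 6, 8 | 2.4% | 66.2% |
| 2, 4, 6 | 3.5% | 68.6% |

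Varying the size removes most of the certain predictions and leaves the best-guess rate about where it was.

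**Timing.** Eight weeks of intervention plus 12 months of follow-up is about 14 months. If all follow-up is to finish by June 2020, the last randomisation falls at about April 2019.

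**The case against.** The strongest reply is that the referring clinician does not control the randomisation slot. After the approach come about a week before consent, the researcher's eligibility assessment and the baseline measures, which include six days of experience sampling. That is at least 7 + 6 = 13 days if the steps run in sequence. Meanwhile another patient may take the predicted slot, or the referred patient may decline or prove ineligible. The stratum itself depends on UHR/FEP status, which the researcher's assessment settles. Four of the five centres pool two to four services, and nothing says a clinician sees allocations at other institutions. CBTp is offered only at some sites, so its exclusion need not reveal the arm everywhere. Adjustment for baseline distress also reduces bias from selection on severity.

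Most of this stands, and it is why the point is modest. It does not remove the risk where one service supplies a stratum, as The Hague appears to. Nor do these steps stop a clinician from holding back or timing a referral on a better-than-chance guess.

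A reader might infer that unblinded clinicians can foresee allocations because the block size was published during recruitment. The documents do not support that. Clinicians' knowledge of allocations is a reasonable inference, not a statement. Knowledge of the whole stratum is nowhere indicated. The text gives no publication date, so whether patients were still being randomised when the article appeared cannot be settled.

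**Conclusion.** The point holds as a minor weakness in allocation concealment. Staff who know the block size, its boundaries and every earlier allocation in a stratum would be certain of about 20% of allocations and guess 66% correctly. The corresponding figures in complete blocks, 25% and 68%, are also upper bounds. For a clinician who sees one of several pooled services, 53–56% is the more realistic range.

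These results assume equal strata of 15, services of equal size within a centre, and treating staff who learn the arm of their own patients. They measure how predictable allocation is. They do not show that any selective referral took place or how large a resulting bias would be. The article contains no contradiction or wrong figure here; what can be improved is the choice of a single block size.

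**What to change.** For any allocations still to be made, the independent researcher should regenerate the unused part of the list with randomly varying block sizes (for example 4, 6 and 8) within the same ten strata. The scheme should be withheld from sites and from everyone who approaches or enrols participants. Withholding carries as much weight as varying, because varying alone leaves a fully informed observer's best guess at about 66%.

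The cost is regenerating that part of the list and accepting slightly looser balance within strata. Sample size, analysis model and stratification factors stay as they are. The gain shrinks with the number of allocations left; if none remain, there is nothing to change.

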### Assessment of safety

We will monitor and record any serious adverse events throughout the entire study period. These are any serious untoward incidents that result in death, persistent or significant disability or incapacity, require (extension of) hospitalisation or are life-threatening. Serious adverse events are not expected to occur as a result of the intervention. All serious adverse events will be reported to the accredited Medical Ethics Review Committees (MERC). If there are concerns about unexpectedly high rates of serious adverse events, this will be investigated further in interim analyses and if this yields any safety or ethical concerns the Trial Management Committee will terminate the trial prematurely.

### Statistical analysis

The investigators will access the final trial dataset to test the primary hypothesis of a reduction in distress associated with psychotic experiences measured with the CAARMS using a linear regression model with distress at all three time points (i.e. post-intervention, 6-month and 12-month follow-ups) as the dependent variable and distress at baseline, condition (ACT-DL + TAU vs. TAU), time (as a three-level factor), centre (as a five-level factor), the baseline × time interaction, and the condition × time interaction as independent variables, according to the intention-to-treat principle. Within-subject clustering of repeated measures will be taken into account by allowing residuals within subjects to be correlated with a completely unstructured variance-covariance matrix.

The model will be fitted using restricted maximum likelihood estimation using Stata 15 [85]. This will allow for the use of all available data under the assumption that data is missing at random and if all variables associated with missing values are included in the model [86, 87]. Hence, bias due to attrition over time, due to difference between groups, or as a function of baseline distress is already mitigated by the model. Potential bias due to missing outcomes will be assessed in descriptive analyses of baseline characteristics stratified by missing data for the primary outcome and condition as follows: (a) experimental condition with no missing primary outcome at post-intervention time point, (b) experimental condition with missing primary outcome at post-intervention time point, (c) control condition with no missing primary outcome at post-intervention time point, and (d) control condition with missing primary outcome at post-intervention time point [88, 89].

The main effect of condition will be tested via an omnibus test of no difference between the two conditions at all three time points (Wald-type test with df = 3 and alpha = .05). Should the omnibus test be statistically significant, then the three time-specific contrasts will be examined to determine at which time points significant differences are present (each tested at alpha = .05). Secondary hypotheses and analyses of process measures to assess putative mechanisms of change will be tested following the same steps. Given that block randomisation will be carried out in blocks of six participants, with stratification for centre and group, all analyses will include centre and group as covariate, even though there is little reason to expect noteworthy clustering of outcomes by centre.

In addition, multilevel mediation analysis will be used to test indirect effects of condition on primary outcomes (distress associated with psychotic experiences) and secondary outcomes (psychotic experiences, psychopathology, social functioning) via pathways through putative mechanisms of change (psychological flexibility, stress sensitivity, reward experience). Multilevel mediation models will be fitted in MPlus, Version 7 [90], to control for within-subject clustering of multiple time points [91, 92], using the MLR estimator, which allows for the use of all available data under the assumption that data is missing at random (if all variables associated with missing values are included in the model). In a two-level model, multiple time points (level 1) will be treated as nested within subjects (level 2). The total effect of condition (level 2) on primary/secondary outcomes (level 1) will be apportioned into direct and indirect (or, synonymously, mediating) effects through putative mechanisms of change (level 1) using the product of coefficients strategy. This strategy quantifies the point estimate of the indirect effect as the product of the coefficient of independent variable on mediator variable (path a) and the coefficient of mediator variable on dependent variable (path b). We will use statistical software by Selig and Preacher [93] for computing Monte Carlo confidence intervals and assessing the statistical significance of indirect effects, given their advantages over rival methods in the context of multilevel mediation models [93, 94].

For analysis involving ESM variables, multiple ESM observations (level 1) will be treated as nested within time points (baseline, post-intervention, 6-month follow-ups) (level 2) and time points as nested within subjects (level 3). Consistent with established credibility criteria [48], we will further test the effects of ACT-DL in UHR compared with FEP individuals in a-priori planned subgroup analyses. For subgroup analyses comparing UHR and FEP, data on the group variable (UHR, FEP) will be measured prior to randomisation (to address the criterion that the subgroup characteristic is measured at baseline) to investigate whether there is a difference in the reduction in distress associated with psychotic experiences measured with the CAARMS of large effect size between UHR and FEP participants (to address the criterion that the expected difference/effect size is specified a priori) given that only a large effect size would be relevant for implementation of ACT-DL in routine care. It will further be examined whether this effect is (a) consistent across (primary and secondary) outcomes and (b) supported by indirect evidence on putative mechanisms of change (psychological flexibility, stress sensitivity, reward experience). In more exploratory sensitivity analyses, we will compare ACT-DL + TAU, CBTp + TAU and TAU only to investigate whether the reduction in distress associated with psychotic experiences measured with the CAARMS will be greater for CBTp + TAU than TAU only as well as for ACT-DL than CBTp.

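### Read as a chi-square test, the primary 3-df Wald test after unstructured REML runs at about 6% rather than the declared 5%: a minor excess, removed by naming a small-sample F test

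*Protocol article*

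**What the plan says.** All of this is in the protocol article.

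- **Model (Statistical analysis).** Distress at the three follow-up visits is regressed on baseline distress, condition, time, centre, baseline × time and condition × time. Group (UHR or FEP) is added as a covariate later in the section. Repeated measures are handled by "allowing residuals within subjects to be correlated with a completely unstructured variance-covariance matrix".
- **Estimation (Statistical analysis).** "The model will be fitted using restricted maximum likelihood estimation using Stata 15". No method for degrees of freedom is named.
- **Primary test (Statistical analysis).** The condition effect is tested by "an omnibus test of no difference between the two conditions at all three time points (Wald-type test with df", where the bracket describes a "Wald-type test with df = 3 and alpha = .05" and nothing more. The three time-specific contrasts, each at .05, are examined only if this test is significant. Secondary outcomes and process measures follow the same steps.
- **Sample size.** The test is set "against the two-sided alternative hypothesis that there is a difference at one (or more) of the three follow-up time points". The plan recruits "participants (75 per arm) at baseline to the study, which allows for a 31% attrition rate"; the total is 150, of whom 104 are expected to remain. These are to suffice "to detect a medium effect size of *d* = 0.5 at (at least) one of the post-intervention and follow-up time points". The claim made for that number is detection "with a power of 0.92 when testing at alpha = 0.05".

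**The concern.** An unstructured covariance over three visits has six parameters, all estimated from the same data as the treatment effects. A chi-square reference ignores that estimation error. With complete data the 3-df Wald statistic from this model follows a scaled Hotelling T-squared distribution, whose upper tail is heavier than that of chi-square with 3 df. At around 100 participants the difference is small but can be measured.

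This matters because the omnibus test is the trial's single confirmatory test and the gate to the time-specific contrasts. The article states the test, its df and its alpha. If the test is run as that text most naturally reads, the three do not agree at the planned sample size.

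**Working it through.** **Inputs from the article.** 150 randomised 1:1 in blocks of six, stratified by five centres and two groups; 31% attrition; d = 0.5; alpha .05; 3 df; REML with a 3 × 3 unstructured covariance; covariates as listed above.

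**Assumptions, not in the article.** Equal correlation rho between all pairs of visits, normally distributed outcomes, dropout unrelated to outcome, and, for the rising-loss scenario, cumulative loss of 10%, 21% and 31%.

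**1. The plan's own figures.** 150 × 0.69 = 103.5, so 104; 75 × 0.31 = 23.25, so 23 lost per arm. For power, take d = 0.5 at all three visits and condition on baseline. The noncentrality is then (N/4) × d² × 3 / [(1 − rho)(1 + 3 rho)]. At rho = 0.5 this is 26 × 0.25 × 3/1.25 = 15.6. Power against the chi-square cutoff of 7.815 is:

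| rho | power |
|---|---|
| 0.2 | 0.921 |
| 0.3 | 0.910 |
| 0.4 | 0.913 |
| 0.5 | 0.928 |

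The stated 0.92 is reproduced to within about 1 point.

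**2. Exact type I error with complete data.** With nu residual degrees of freedom, the chance of exceeding 7.815 under the null is P[F(3, nu − 2) > 7.815 (nu − 2)/(3 nu)].

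| Situation | nu | Type I error |
|---|---|---|
| 104 completers, all covariates (104 − 8) | 96 | 6.03% |
| 104 completers, intercept, condition and baseline only (104 − 3) | 101 | 5.98% |
| 150 completers, all covariates (150 − 8) | 142 | 5.69% |
| 150 completers, intercept, condition and baseline only (150 − 3) | 147 | 5.66% |

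**3. The 5% cutoff.** This is 3 nu/(nu − 2) × F(0.95; 3, nu − 2). At nu = 96 it is 8.28. The chi-square p-value at 8.28 is .041, so the choice of reference matters only for chi-square p-values between about .04 and .05.

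**4. Simulation of the planned model.** 60,000 null trials per scenario (Monte Carlo standard error 0.1 point), with REML, unstructured covariance, all listed covariates and stratified blocks of six.

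| Scenario | Chi-square reference | Hotelling-scaled F |
|---|---|---|
| 104 complete, rho 0.5 | 6.15% | 5.15% |
| 150, 31% lost at every visit, rho 0.5 | 6.02% | 5.02% |
| 150, rising loss, rho 0.3 | 5.74% | 4.78% |
| 150, rising loss, rho 0.5 | 5.92% | 4.92% |
| 150, rising loss, rho 0.7 | 6.09% | 4.98% |
| 150, no loss, rho 0.5 | 5.62% | 4.94% |

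Under the planned attrition the chi-square version therefore runs at 5.7% to 6.2%.

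**5. Time-specific contrasts.** A single 12-month contrast referred to the normal distribution rejected in 5.2% to 5.4% of the same simulated trials. The interval multiplier is 1.960 against 1.985 for t with 96 df; 1.985/1.960 = 1.013, so intervals are about 1% too narrow.

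**The case against.** The strongest objection is that the error is inferred. The article never says chi-square, and a Wald F test also has 3 numerator df. The df method is the kind of detail a journal article leaves to the analysis plan or the code, and Data Availability says the full protocol and code can be had on request. This stands in part: the point is conditional on the chi-square reading, and silence on a df method alone would be no finding. But the article goes beyond silence. It gives a complete-looking specification with a single df, and that specification does not deliver the stated alpha.

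The second objection is size, and it stands in full. The excess is about 1 percentage point; design, estimand and sample size are untouched.

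A reader might also infer two stronger things, neither of which is supported:

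- *That the inflation is worse in the UHR-by-FEP comparison because its cells are smaller.* It depends on the residual df available to estimate the covariance, not on cell size. The article plans a comparison of effects between the groups. As an interaction in the pooled model with 104 completers, even nu = 93 gives 6.07%. A simulation of 40,000 null trials gave 6.00% for the interaction and 6.02% for the main effect.
- *That every secondary outcome and process measure inherits the same error.* ESM measures have no 12-month assessment (Outcomes) and are analysed in a three-level model (Statistical analysis), so the argument from 3 df and six covariance parameters does not carry over to them.

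**Conclusion.** The point holds as a minor one. If the omnibus statistic is referred to chi-square with 3 df, the primary test has a true type I error of about 6% under the planned attrition, and the excess does not vanish without attrition. The exact formula and the simulation agree, and the result moves little with the assumed correlation or dropout pattern. Time-specific contrasts are barely affected.

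The conclusion rests on the chi-square reading, normal outcomes and ignorable dropout; skewed outcomes are not covered. If the unseen analysis plan already names a small-sample method, the inflation largely disappears and what remains is a wording mismatch.

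**What to change.** In Statistical analysis, replace the 3-df Wald test with a small-sample F test with 3 numerator df, using REML with Kenward-Roger degrees of freedom. Apply it to the omnibus test, the time-specific contrasts and their intervals, for the primary outcome and for the non-ESM continuous outcomes analysed with the same model. Stata 15's mixed command offers this through its dfmethod option. If the analysis plan already says so, align the article's text with it. Settle this before unblinded data are analysed, so that the reference distribution is not chosen after a borderline result.

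The cost is one clause and a little power. At n = 104 with d = 0.5 at all three visits, referring the test to F(3, 94) takes power from 0.928 to 0.916 at an assumed rho of 0.5, and from 0.921 to 0.909 at 0.2, a loss of 1 to 2 points. The simulated correction in the working was the Hotelling-scaled F, which brought the error to 4.8% to 5.2%. Kenward-Roger itself was not simulated, so a short null simulation with the trial's own code would be a sensible check.
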